### Users (≥ 60 years old)

Describe the characteristics of older adults including the prevalence of frailty and losses of intrinsic capacity.Identify the possible association between the ICOPE framework and VIG-Frail in individuals aged 60 and older.Investigate the possible association between the ICOPE and selected Nursing Outcomes Classification (NOC) indicators in individuals aged 60 and older.Analyse the impact of the program on their knowledge of their health status, lifestyle, risk factors of chronic conditions, community-based health assets and satisfaction.

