**Methods:**

Research protocol for Service-Learning program with a mixed methodology and experimental intervention design, involving undergraduate students from Nursing, Physiotherapy, Human Nutrition and Dietetics, Occupational Therapy and Psychology degrees, and older adults from the community over 60 years old. The intervention at the university, consisting of three sessions, will be based on CGA. Student data will be collected during the final session using the questionnaire developed and validated by León-Carrascosa et al. (2020) to evaluate Service-Learning in higher education. After the first and last session, an additional questionnaire will assess satisfaction and perceived competency development. Older participants will be assessed with VIG-Frail, Integrated Care of Older People (ICOPE) screening tool, EuroQol 5D-5L, Nursing Outcomes Classification and sociodemographic data. They will complete a post intervention questionnaire regarding their satisfaction, perceived health status, knowledge of healthy lifestyle habits, and awareness of community resources, whose items will be evaluated using a 5-point Likert scale. Data will be collected through the REDCap platform and analysed using SPSS. Qualitative data from focus groups will undergo thematic analysis.

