## Research aims

The general objective of this study is to evaluate the impact of a Service-Learning program that brings undergraduate health students into contact with community-dwelling older adults, assessing its benefits for students’ professional development and for older adults’ knowledge regarding their health.

Based on this general objective, the study addresses several specific goals for both students and older adults that operationalize the evaluation of the programme’s impact.

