## Methods/design

### Aim, design and setting of the study

The study was registered in *Clinical Trials* with the registration number NCT06890325 on March 24, 2025 (https://clinicaltrials.gov/study/NCT06890325). It is a one-arm intervention study that employs a single-centre mixed-methods approach, following the experimental mixed-methods framework outlined by Creswell and Creswell (2018) [39]. The study aims to analyse undergraduate health students’ perceptions of their professional training through the Service-Learning methodology, focusing on three dimensions: formative, learning, and service. This community-based educational approach also contributes to enhancing health knowledge among participants aged 60 years and older.

The study will be carried out in the Osona region (Barcelona, Spain), at the University of Vic-Central University of Catalonia (UVic-UCC), in collaboration with various community centres including primary care centres, neighbourhood associations and social organisations within the local community, such as Equip d’Assitència Primària Vic - CAP El Remei Vic sud, ASHES – Associació per a la Sostenibilitat Humana, Ecològica i Social, the Associació de Veïns Horta Vermella, and the Germanetes dels Pobres de Vic.

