##### Older adults

A specific questionnaire was also developed for community dwelling older adults to evaluate their perceived knowledge of their own health status, their awareness of lifestyle habits and modifiable risk factors, their understanding of community health resources and assets, and their overall satisfaction with the experience. This questionnaire will be completed at the end of the final session. Detailed questions are available in the supplementary file.

All items for both target populations will be rated on a 5-point Likert scale (1 = “not at all” to 5 = “very much”). All questionnaires will be created and administered through the REDCap platform. Research team members have undergone prior training to ensure their standardized administration and the accuracy of data collection.

In addition to the self-reported questionnaire, several validated instruments will be used to assess the health status of the older adults. The instruments include ICOPE tool to assess intrinsic capacity [16], the validated VIG-Frail scale to evaluate frailty status [41], the EuroQol-5D-5L to measure quality of life and eighteen indicators of NOC. The EuroQol-5D-5L is a widely used instrument validated for measuring self-perceived health and quality of life and has normative reference values for the Spanish population [42, 43].

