For the limitations, a risk management plan has been developed to address them. One anticipated challenge is participant recruitment, which may be mitigated through collaboration with key community organizations or by offering visits at user locations. Another potential limitation is the non-attendance of older adults on session days; this may be addressed by converting the session into a role-play, practical workshop, clinical case discussion, or report preparation. The absence of a control group may limit the evaluation of intervention effectiveness. On the other hand, the specific objectives of the assessment of students’ soft skills and older adults’ knowledge is based on self-perceived evaluations, which may limit the validity of the results. Additionally, no pre-post test will be administered, which could reduce the reliability of the findings. No imputation methods will be applied for missing data, only complete-case analysis will be performed, acknowledging that this approach may reduce the statistical power of the results. Lastly, logistical challenges may arise, such as managing space, scheduling, and ensuring multidisciplinary interaction among student groups.

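### The objective of analysing impact on older adults' knowledge rests on one post-programme questionnaire in a single arm, which cannot show the size or direction of any change

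*Protocol article*

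**What the plan says.** **Objective.** Research aims states the general objective as evaluating the programme's impact, "assessing its benefits for students’ professional development and for older adults’ knowledge regarding their health". The fourth goal for users aged 60 and over begins "Analyse the impact of the program on their knowledge of their health status" and goes on to lifestyle, risk factors, community resources and satisfaction. The Abstract (Background) repeats the general objective. Aim, design and setting adds that the approach helps to raise health knowledge in this group.

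**Design.** The same section says: "It is a one-arm intervention study that employs a single-centre mixed-methods approach".

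**Measurement.** Under Data collection methods, Older adults, a purpose-built questionnaire is used "to evaluate their perceived knowledge of their own health status, their awareness of lifestyle habits and modifiable risk factors", together with understanding of community resources and satisfaction. Items are scored 1 to 5. On timing: "This questionnaire will be completed at the end of the final session". The Abstract (Methods) agrees: "They will complete a post intervention questionnaire regarding their satisfaction, perceived health status, knowledge of healthy lifestyle habits, and awareness of community resources". The session 1 battery in Structure of the intervention consists of sociodemographic data, preferences and expectations, ICOPE, VIG-Frail, EuroQol-5D-5L and NOC indicators. It contains no knowledge measure.

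**Analysis.** Statistical analysis names no comparison for this outcome. Only the general provision for descriptive statistics covers it.

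**Limitations.** The Discussion accepts that lacking a control group may restrict what can be said about effectiveness and that self-perceived measures may weaken validity. It adds that "no pre-post test will be administered, which could reduce the reliability of the findings".

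**The concern.** Impact on knowledge is a statement about change, or about a difference from what would have happened without the programme. Either needs a reference: the same people beforehand, or comparable people without the programme. The plan has neither for this outcome. A favourable mean after the final session would be reported under an impact objective although the data do not show whether knowledge rose, stayed level or fell.

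Recruiting more people does not help, because what is missing is a quantity and not precision. The loss is also permanent for each participant: once someone has been through session 1, a true baseline can no longer be collected. Trial registration states that enrolment had begun before 24 March 2025, so this already applies to some participants.

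The point concerns the older-adult half of the general objective. It does not extend to the student objectives.

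**Working it through.** The plan gives no figure for this outcome to reproduce. Its one sample-size figure, 304 in Power calculation, has no population, effect size, SD or test attached and is described as a starting value to be adjusted. It cannot be checked against this objective.

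**Step 1: what the planned data identify.** Inputs: a 1-5 response scale, one measurement after the programme, one arm. Let m be the post-programme mean and b the unmeasured baseline mean in the same people. The mean change is d = m - b. Nothing is known about b except that 1 ≤ b ≤ 5, so

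m - 5 ≤ d ≤ m - 1.

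| Post-programme mean m | Lowest possible change | Highest possible change |
|---|---|---|
| 3.5 | 3.5 - 5 = -1.5 | 3.5 - 1 = +2.5 |
| 4.0 | 4.0 - 5 = -1.0 | 4.0 - 1 = +3.0 |
| 4.5 | 4.5 - 5 = -0.5 | 4.5 - 1 = +3.5 |

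The interval is always (m - 1) - (m - 5) = 4 points wide, which is the full span of the scale. It contains zero for every m from 1 to 5. The number of participants does not enter the expression. The values of m are examples.

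**Step 2: what a baseline would add.** If the same items were also given before the programme, the 95% CI half-width for mean change would be 1.96 × SD × √(2(1 - r)) / √n, where r is the pre-post correlation. The document gives no SD, no r and no number of older adults, so all three are assumptions: SD 0.8 to 1.2, r 0.3 to 0.7.

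- n = 50: from 1.96 × 0.8 × √0.6 / √50 = 0.17 to 1.96 × 1.2 × √1.4 / √50 = 0.39 points.
- n = 100: from 1.96 × 0.8 × √0.6 / √100 = 0.12 to 1.96 × 1.2 × √1.4 / √100 = 0.28 points.

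These figures show only that change becomes estimable. They do not forecast this study's precision.

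**Step 3: what a baseline would not add.** With one arm, d mixes any programme effect with secular change and expectancy. A paired estimate is of uncontrolled change, and attributing it to the programme needs further assumptions.

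**The case against.** **The limitation is disclosed.** This is largely true. The Discussion concedes limits on effectiveness, validity and reliability, so it would be wrong to say that the authors hide the weakness or mention reliability alone. However, each concession is put as something that may weaken the findings, while the actual consequence is that a quantitative effect is not identified. The objectives still promise impact.

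**The study is mixed-methods.** Focus groups with older adults are planned to explore perceived effects on their health knowledge and on awareness of community resources. A reader might infer that the impact objective would have no support at all. That goes too far: there is a second planned source. It consists of volunteers' accounts and can describe perceived change, but it cannot estimate it.

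**The items are not shown.** The supplement may contain questions on perceived change, and the response anchors would suit either type of item. The article's description points to levels of knowledge, awareness and understanding, but does not settle the matter. If the items ask about change, the bounds in Step 1 do not apply to them, although self-rated change would remain weak evidence.

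**Bounds are not probabilities.** A reader might infer that a high final score is equally consistent with gain and decline. The bounds show what is possible, not what is likely: with m = 4.0, a change of -1.0 would require every participant to have scored 5 beforehand.

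**A baseline is not free.** The common assessment block of 20 to 30 minutes is already full, and participants past session 1 cannot supply one. Both points stand and limit the remedy, but neither removes the mismatch.

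**Conclusion.** The concern holds in a qualified form. The plan sets an impact objective for older adults' knowledge, and its planned quantitative data cannot give the size or sign of a change. The uncertainty covers the full 4 points of the scale's range and does not shrink with sample size. This rests on two conditions: that the supplementary items measure perceived knowledge and not perceived change, and that no knowledge measure is taken at session 1. The article states the second; its description supports the first without proving it.

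Two stronger readings are not supported. One is that a session 1 baseline would by itself establish impact. It would not, since the study has no comparison group. The other is that the precision of a pre-post comparison can be derived from the 304 in Power calculation by treating it as a number of students and dividing by group size. The article does not say that the 304 are students, sets groups at up to five, and gives no number of older adults.

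**What to change.** 1. **Add a baseline where it is still possible.** For participants who have not yet passed session 1, give the same perceived-knowledge items (health status, lifestyle and risk factors, community resources; not satisfaction) at the start of that session, before the assessment block. Report paired change with a 95% CI and the number with both measurements, since the plan uses complete cases only.
2. **Earlier participants (optional).** A retrospective rating of knowledge before the programme can be added beside each item. It must be reported separately and labelled as open to recall and social-desirability bias.
3. **Qualify the wording in either case.** In the Abstract (Background), Research aims, the goals for users aged 60 and over, and Aim, design and setting, refer to uncontrolled change in perceived knowledge if a baseline is added. Otherwise, say that the study will describe perceived knowledge after the programme.
4. **Correct the limitation.** State in the Discussion that a programme effect on older adults' knowledge is not identified by this design, and that the focus groups contribute descriptive accounts of perceived change.
5. **Settle the item type.** If the supplementary items do ask about perceived change, say so in the main text and describe the outcome as self-rated change.

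**Cost.** A few more minutes in session 1, one additional REDCap form and edits to the wording. Seeing the items twice may sensitise participants slightly, and secular and expectancy effects remain uncontrolled. Items 3 to 5 need no new data and are the minimum.

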## Methods/design

### Aim, design and setting of the study

The study was registered in *Clinical Trials* with the registration number NCT06890325 on March 24, 2025 (https://clinicaltrials.gov/study/NCT06890325). It is a one-arm intervention study that employs a single-centre mixed-methods approach, following the experimental mixed-methods framework outlined by Creswell and Creswell (2018) [39]. The study aims to analyse undergraduate health students’ perceptions of their professional training through the Service-Learning methodology, focusing on three dimensions: formative, learning, and service. This community-based educational approach also contributes to enhancing health knowledge among participants aged 60 years and older.

The study will be carried out in the Osona region (Barcelona, Spain), at the University of Vic-Central University of Catalonia (UVic-UCC), in collaboration with various community centres including primary care centres, neighbourhood associations and social organisations within the local community, such as Equip d’Assitència Primària Vic - CAP El Remei Vic sud, ASHES – Associació per a la Sostenibilitat Humana, Ecològica i Social, the Associació de Veïns Horta Vermella, and the Germanetes dels Pobres de Vic.

### Characteristics of participants or description of materials

The study comprises two population groups: university students and older adults. Students will be recruited from five undergraduate programs at UVic-UCC (Nursing, Physiotherapy, Human Nutrition and Dietetics, Occupational Therapy, and Psychology), specifically those enrolled in courses focused on ageing-related topics.

Participants aged 60 and above who can travel independently or with caregiver support to the UVic-UCC facilities will be eligible to participate. Individuals presenting cognitive impairment or significant communication difficulties will be excluded to ensure adequate understanding and participation in the intervention. Throughout the study, participants will remain under their usual care, since the intervention is designed to be compatible with and not a substitute for standard treatment. Recruitment will be through key associations and institutions in the Osona region. Snowball sampling and social media will also be used for participant enrolment.

The sampling performed is non-probabilistic and either consecutive or convenience-based, according to the criteria described above. The project will be presented at various community associations. Regarding the students, they will be recruited through the participating courses of the previously mentioned university degree programs.

### Description of all processes, interventions, and comparisons

#### Structure of the intervention

The intervention will consist of three sessions, during which older adult participants will come to the university (Fig. 1). During the first visit, all older adults will meet at a designated meeting point with the professor, also the purpose and procedures of the intervention will be reviewed, and participants will be invited to participate in the study and asked to sign the informed consent form. Approximately 12–20 students will be present in the classroom, divided into groups of up to 5 students per each older adult as stated in Order SSI/81/2017 published in the Spanish Official State Gazette (BOE). A maximum ratio of five students per user is established in order to prevent an excessive number of students per participant, thereby ensuring the quality of learning and, most importantly, safeguarding the patient’s right to privacy and comfort [40].

**Fig. 1 Fig1:**
[figure not shown]
Description of the intervention process

The welcome session will last approximately 5 to 10 min, after which each group will be guided to their assigned classroom. The first session will include a common assessment block based on CGA lasting 20 to 30 min. This block includes the collection of sociodemographic data (age, gender, education level, neighbourhood/area of residence, whether the participant requires a caregiver or is a caregiver, last occupation, and current living situation). Participants will also be asked about their preferences, values, priorities, and social context, as well as their expectations for the intervention.

Within this common block, various tests will be administered: ICOPE, VIG-Frail, EuroQol-5D-5L and indicators of Nursing Outcomes Classification (NOC). Following this, a specific assessment block will last approximately 5 to 10 min. This specific block will include a questionnaire or test aligned with the learning objectives and competencies of each subject, which may vary depending on the subject participating in the project. The data collected in this subject-specific block will not be used for research purposes; it will be used exclusively by the students to complete their reports. After each session, participants will be dismissed, and a debriefing session will be held with the students.

The next session will consist of a classroom-based student activity (without the older adults). During this session, students will prepare a report based on the CGA and will develop personalized health recommendations for the older adult, including health education strategies and suggestions for referral to appropriate community health assets and programs. The report will include: (1) a summary table of the common block results and key domains: frailty (VIG-Frail score), quality of life (EUROQOL-5D-5L), cognition, mobility, nutrition, vision, hearing, psychological status, social support, caregiver status, and urinary incontinence-interpreted based on the ICOPE and NOC responses; (2) a section on the (subject-depending) specific block, detailing the test used, its purpose, and results; and (3) a section with personalized health promotion and prevention recommendations, including community-based health resources aligned with the participant’s preferences and place of residence. All reports will be reviewed by the course professor and the project coordinator. This dual review process helps ensure the quality and consistency of the content before it is shared with the users.

The final session will include the visit from older adults. To improve adherence to the intervention plan, reminder phone calls will be made to participants before this session. During this visit, students will meet again at the university with the same older adults they assessed during the first visit and present the personalized health report prepared in class. The main objective of this session will be for students to explain their findings and recommendations, applying personalized recommendations to the specific case of the older adult. In cases where the participant is unable to attend the session in person, data collection will be conducted via telephone.

At the end of the intervention of each semester, focus groups with students, professors, and older adults will be conducted to explore their experiences and perceptions of the programme. Further details on the procedures and data collection methods for these focus groups are provided in the Data Collection Methods section.

#### Data collection methods

The instruments included in the study are presented in two distinct blocks: one referring to the tools administered to students and another to those applied to the older adult participants.

##### Students

A validated questionnaire developed by León-Carrascosa et al. (2020) is used to evaluate the students’ perceptions of the Service‑Learning methodology in higher education. The questionnaire consists of 29 items distributed across three dimensions that reflect the core components of Service-Learning: the formative aspect as an educational goal, the learning process as a means, and the service component as a commitment to the community. Each item is rated on a Likert-type scale ranging from 1 (strongly disagree) to 5 (strongly agree). The instrument has demonstrated adequate psychometric properties in terms of validity and reliability and has been previously applied in university contexts related to health and social education. The questionnaire will be self-administered by the students at the end of the third session.

An additional questionnaire was specifically developed for this research to assess students’ perceived acquisition of knowledge and competencies related to health promotion, disease prevention, CGA, and Intrinsic Capacity. It also includes items addressing transversal skills such as critical thinking, and problem solving, as well as perceived integration of knowledge and overall satisfaction with the project. Items were formulated in neutral language to minimise response bias related to positively or negatively loaded wording. The questionnaire will be self-administered at the end of the first and last sessions. As each session focuses on a different learning domain, the two assessments correspond to distinct sets of competencies rather than repeated measures of the same construct. Detailed items can be found in the supplementary material.

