### Students

Analyse undergraduate health students’ perceptions of their professional training through the Service-Learning methodology, focusing on three interrelated dimensions: the formative development as an educational goal, the learning process as a means, and the service component as a commitment to the community.Identify distinct student profiles based on their responses to the Service-Learning questionnaire through a cluster analysis, and to examine how these profiles differ according to sociodemographic variables: age, sex, and university degree.Describe the impact of the Service-Learning intervention on soft skills: communication, interdisciplinary teamwork, and critical thinking.Describe the impact of the Service-Learning intervention on specific competencies related to Comprehensive Geriatric Assessment and Intrinsic Capacity.Compare students’ satisfaction levels, competences, and soft skills across different sessions.

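### Student competencies rated after session 1 have no quantitative rating at the end of the programme, although the objectives concern the whole intervention

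*Protocol article*

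**What the plan says.** Under *Research aims – Students*, the fourth objective is to "Describe the impact of the Service-Learning intervention on specific competencies related to Comprehensive Geriatric Assessment and Intrinsic Capacity". The third uses the same wording for soft skills. The fifth is to compare satisfaction, competences and soft skills between sessions.

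Under *Data collection methods – Students*, a questionnaire written for this study covers perceived knowledge and competencies, transversal skills, integration of knowledge and satisfaction. On timing: "The questionnaire will be self-administered at the end of the first and last sessions". The protocol reasons that each session has its own learning domain, and concludes that "the two assessments correspond to distinct sets of competencies rather than repeated measures of the same construct". The items themselves are in supplementary material.

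*Structure of the intervention* sets out three sessions. In the first, students carry out the assessment: "The first session will include a common assessment block based on CGA lasting 20 to 30 min". In the second, a class without the older adults, "students will prepare a report based on the CGA and will develop personalized health recommendations for the older adult". In the third they meet the same older adult again: "The main objective of this session will be for students to explain their findings and recommendations".

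**The concern.** A design that measures only after the intervention still has to take its measurement once the intervention is complete. If the two questionnaires share no competencies, the first set is rated when only the opening session has taken place. Reporting that rating as the programme's impact would credit the whole programme with what students felt after one visit. Their confidence may rise or fall when they have to interpret the results, write recommendations and explain them to the person assessed. The planned ratings of that set could not show either change.

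**Working it through.** The protocol gives no figure on this point, so the check sets the measurement schedule against the session content and the objectives.

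| Session | What students do | First competency set | Last-session competency set |
|---|---|---|---|
| 1 | Administer the CGA-based block | rated at the end | not rated |
| 2 | Interpret results, write report and recommendations | not rated | not rated |
| 3 | Present report to the older adult | not rated | rated at the end |

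1. **Count.** The first set has one rating, after 1 of 3 sessions. The number of sessions following its only rating is 3 − 1 = 2. The last-session set has one rating, after 3 of 3. On the protocol's statement, no competency has both an early and an end-of-programme rating.

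2. **Do the later sessions bear on the same field?** Yes. The session-2 report is built on the CGA and interprets the intrinsic-capacity domains from the ICOPE and NOC responses, and session 3 consists of explaining those findings. The *Background* describes CGA as a diagnostic process leading to a judgement on frailty and geriatric syndromes, so interpretation belongs to it. CGA work does not end with session 1.

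3. **Does another instrument fill the gap?** The validated 29-item questionnaire is completed at the end of session 3 but measures perceptions of the Service-Learning method. The end-of-semester focus groups ask in general terms whether the programme influenced knowledge and competencies, but they are voluntary and qualitative. Neither re-measures the session-1 items.

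4. **Is the gap acknowledged?** The limitations paragraph of the *Discussion* concedes that there is no pre-post test, no control group and only self-perceived outcomes for these objectives. A missing pre-post test is chiefly a missing baseline. That one set is rated before most of the programme has happened is not stated.

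5. **If the distinct-sets sentence is loosely worded.** The fifth objective presupposes something comparable at both sessions. If the competency items do recur, the timing gap closes, but the sentence is then wrong and must be corrected. If they do not recur, the gap stands, and any comparison of competences between sessions mixes session with item content. Either way the two sections must be reconciled.

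**The case against.** The strongest objection is that the content of the first set is unknown. It might cover administering the tools, with the last set covering interpretation and communication. Each skill would then be rated straight after it is practised, and the CGA objective would have some end-of-programme data. Rating a skill right after the session that teaches it is a recognised choice that limits recall error, and the protocol gives that kind of reason. This stands as a defence of keeping the session-1 rating. It does not make that rating a measure of the whole intervention.

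A reader might infer that the CGA competencies are the ones left without an end rating, or that the soft-skills objective is mistimed as well. The document supports neither. The sentence speaks of competencies; transversal and satisfaction items may appear at both sessions, and communication could well be asked about in the last one.

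It would also be too strong to say that all information on later change is lost, since the focus groups may bring some of it out.

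Finally, the objectives say only *describe*, and the study has one arm and no baseline. A later rating would therefore not establish a causal effect. That is correct, and it limits what the fix can deliver.

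**Conclusion.** The point holds in a limited form. On the protocol's own statement, whichever competencies are in the first set have no quantitative rating after the report-writing and presentation sessions, while the objectives refer to the intervention as a whole. Two of three sessions follow the only rating. That is a count of the schedule and not an estimate of bias; the direction and size of any change are unknown.

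The conclusion assumes that the distinct-sets sentence is literally true of the competency items. It does not depend on which items they are. The objectives concerned are descriptive specific aims, and the validated 29-item questionnaire is unaffected. The change is worth making because it is cheap and brings the measurement into line with the stated objectives. Nothing here undermines the study as a whole.

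**What to change.** - Repeat the session-1 competency items, with identical wording and scale, in the last-session questionnaire.
- Use the last-session ratings for any objective worded as impact of the intervention. Keep the session-1 ratings as the earlier time point, which also gives the fifth objective a like-for-like comparison.
- Amend the distinct-sets sentence to match, and state which items belong to each administration.
- For cohorts already completed, label ratings of those items as *perceived competence after session 1*. This is a practical matter, because the article says that enrolment began before registration on March 24, 2025.

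The cost is a few more REDCap items in a form that students already complete at the last session, a minor amendment, and separate reporting of earlier cohorts. What is gained is a rating taken after the full programme. It remains self-perceived and uncontrolled, with no measurement before the programme, and should be described as such.
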